### Cognitive and neuropsychological assessment tools

#### Token test

Token test is the most widely used clinical tool to assess the presence of aphasia. It consists of 36 items in which the patient is required to understand orders of increasing complexity. It has a good test-retest reliability (46) and intra-rater reliability while the inter-rater one is good although not in all its parts (47).

#### Line bisection test of BIT battery

The Line bisection test allows to assess the presence of neglect. It is performed by presenting the partecipant with a series of horizontal lines and asking him/her to bisect them in the center. If the patient has neglect, he/she will fail to dissect them in the midline. Together with other tests, line bisection is included in the Behavioral Inattention Test (48). It is an easy test to administer and does not require any specific materials.

### Mini-mental state examination

The MMSE test is a practical, well spread, questionnaire including 11 items that aims to evaluate cognitive functions. It has a high sensitivity, a moderate-to-high level of reliability, validity and excellent reliability at test-retest. Indeed it is not completely reliable in assessing mild cognitive impairments (49, 50).

### De Renzi imitation gesture test

It is a test that can be easily administered and that allows with a certain sensitivity to recognize if the patient has ideomotor apraxia (51).

### Beck depression inventory II

The BDI I-II is a valuable tool to detect if the subject is suffering from depression. It is a self-evaluation test and has good internal validity and good test-retest reliability (52).

### Outcome measures

Primary outcome measures will be score changes in two functional scales: FIM and UPDRS. Secondary outcome measures will be changes in kinematic parameters as revealed by gait analysis.

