**Material and methods:**

This study is designed as a prospective randomized controlled trial, with four arms. We estimated a sample size of 64 patients (16 in each treatment group) to be able to detect an effect size of *F* = 0.4 with a statistical significance of 0.05. Primary outcomes will be functional gains in the FIM and UPDRS scales. Secondary outcome measure will be functional gain as revealed by kinematic parameters measured at Gait Analysis.

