### Sample size

The sample size has been defined by the achievement of outcome measures. In this study, our outcome measures are an improvement in motor functions and kinematic parameters of patients suffering from Parkinson's disease, as revealed by means of functional scales (FIM, UPDRS) and gait analysis. In order to detect an effect size of *F* = 0.4 (medium to large effect size, according to Cohen, 1988) (39) with 80% power and 0.05 alpha in a mixed subjects design (4 groups and 3 time points), G^*^Power suggests that a total sample size of 64 participants (16 participants for each group) should be enrolled. We plan a sample size of *N* = 80 (*N* for each group = 20) that will be more than adequate to control for a potential participants' drop out. Furthermore, this sample size will be adequate to ensure that data can be interpreted separately, for each group.

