### Demographic and clinical characteristics

The patients will be classified according to Hoehn and Yahr scale. This classification allows the degree of disability to be assessed on a scale of I to V. Patients classified from stage I to stage III are defined as mildly disabled, while those in stage IV or V are defined as severely disabled (44). The HY scale is widely used in clinical settings to classify the level of disability of Parkinson's patients because it is simple, easily applicable and reliable. It also has a good correlation with the UPDRS scale (45). The anagraphic (age and sex) and clinical characteristics of the subjects will be assessed at T0 (baseline) in all groups to evaluate their homogeneity.

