### Functional independence measure

The FIM scale is widely used in rehabilitation settings to assess the level of assistance a patient needs in performing daily living activities. It includes 18 items with scores ranging from 1 to 7. The items are grouped into six areas, each with a specific competence: 1. self care; 2. sphincter control; 3. mobility; 4. locomotion; 5. communication; 6. social cognition. The maximum score is 126 and represents the total independence of the subject. The minimum score is 18 and represents the subject's total dependence in all activities of daily living (57, 58). It has good inter-rater reliability, although trained personnel are needed to administer it properly (59).

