### Statistical analysis

The statistical analysis of the data will be carried out by a statistician using the R software.

Given the design of the protocol (4 Groups X 3 Time-points), a mixed between-within ANOVA model with Greenhouse-Geisser correction will be used as a statistical test for this purpose. Statistical significance will be set at 0.05 to reject the null hypothesis.

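### FIM and UPDRS are two unranked primary outcomes under a single unadjusted 0.05, with no rule on whether one or both must be significant

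*Protocol article*

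**What the plan says.** The abstract (Material and methods) says "Primary outcomes will be functional gains in the FIM and UPDRS scales", and the Outcome measures section repeats it: "Primary outcome measures will be score changes in two functional scales: FIM and UPDRS". Neither place ranks the scales.

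The Statistical analysis section names one model, "a mixed between-within ANOVA model with Greenhouse-Geisser correction will be used as a statistical test for this purpose", and one threshold: "Statistical significance will be set at 0.05 to reject the null hypothesis". It refers to a single null hypothesis although there are two primary scales.

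The Sample size section makes one calculation, for an "effect size of *F* = 0.4" "with 80% power and 0.05 alpha in a mixed subjects design (4 groups and 3 time points"). It is tied to neither scale. It gives 64 patients (16 per group), raised to 80 (20 per group) for dropout.

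No section gives a hierarchy, an alpha split, a composite, a multivariate test, or a statement that one or both scales must reach significance.

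**The concern.** With two primary outcomes, the per-test significance level equals the trial's error rate only if a rule links the two tests. Without one, a treatment that affects neither scale has two chances to be reported as effective, and the choice of which result carries the claim can be made after the data are seen. The sample size has the same gap, because it is worked out for one test at 0.05. If an adjustment is adopted later, power for each scale will be lower than the article implies.

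**Working it through.** **Inputs from the article.** Two primary scales; alpha 0.05; power 80%; f = 0.4; 4 groups; 3 time points; N = 64 calculated and 80 planned.

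**Inputs assumed.** The article gives neither the correlation between FIM and UPDRS nor the correlation between time points. Ranges are used for both.

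**Step 1: the plan's own figure.** For the between-group test in a repeated-measures ANOVA, the noncentrality is λ = f²·N·m / (1 + (m − 1)ρ), with m = 3 time points and 3 and N − 4 degrees of freedom.

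- ρ = 0.75, N = 64: λ = 0.16 × 64 × 3 / 2.5 = 12.29, power 0.823.
- ρ = 0.80, N = 64: λ = 0.16 × 64 × 3 / 2.6 = 11.82, power 0.807.

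In steps of four patients, 64 is the smallest N that reaches 80% at either value. Other assumptions give other sizes: 52 at ρ = 0.5 and 68 at ρ = 0.9 for the same test, 76 for a one-way ANOVA, and 20 for the group-by-time interaction at ρ = 0.5. So 64 can be reproduced, but not from the stated inputs alone.

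**Step 2: either scale suffices, independent scales.** 1 − (1 − 0.05)² = 0.0975, which is 1.95 times 0.05. Whatever the correlation, the bound is 0.05 + 0.05 = 0.10.

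**Step 3: either scale suffices, correlated scales.** The 4 × 3 design was simulated under no effect on either scale (16 per group, within-patient time correlation 0.5 assumed, 40,000 trials per row, Monte Carlo error about 0.0015).

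| Between-scale correlation | Interaction test | Group-effect test |
|---|---|---|
| 0 | 0.097 | 0.096 |
| 0.3 | 0.097 | 0.093 |
| 0.5 | 0.087 | 0.092 |
| 0.7 | 0.085 | 0.085 |
| 0.8 | 0.081 | 0.079 |
| 0.9 | 0.072 | 0.074 |

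The interaction figure at 0.5 looks like a low draw: the rate for one scale alone in that row was 0.0457 instead of 0.05. The 0.092 beside it is the better guide. With 20 per group the interaction test gives about the same: 0.08 to 0.10 for correlations of 0 to 0.8, and 0.072 at 0.9.

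**Step 4: both scales must be significant.** The simulated rate with no effect on either scale is 0.002 at correlation 0, rising to 0.026 at 0.9. If only one scale has no effect, joint success still requires that scale to reject, so the error is at most 0.05.

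**Step 5: power at 0.025.** The between-group formula of step 1 is used, with the two time correlations that reproduce 64.

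| N | ρ = 0.75 | ρ = 0.80 |
|---|---|---|
| 64 | 0.736 | 0.715 |
| 76 | 0.827 | 0.809 |
| 80 | 0.851 | 0.834 |

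In steps of four, 76 patients are needed for 80% power. If both scales are tested at 0.025, the error for independent scales is 1 − 0.975² = 0.0494, and it is at most 0.05 for any correlation.

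**The case against.** The strongest reply is that the article never says success on either scale is enough. It joins the scales with a plain conjunction and speaks of one null hypothesis, so a both-significant reading is open, and under it there is no inflation. The Statistical analysis section is also a two-sentence summary, and a fuller protocol or analysis plan may hold a multiplicity rule.

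The first part stands: the inflation is conditional and must be reported so. The second stands only in part. The article does not simply leave alpha to another document. It commits to two primaries and to one 0.05 in both the sample size and the analysis. What counts as a positive trial belongs with the definition of the primary outcome.

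A reader might infer four stronger points that the article does not support:

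- **That the error rate is nearly double, as a fact.** This needs the either-scale reading and nearly independent scales. Both scales are taken in the same patients and both cover daily living, so positive correlation is likely.
- **That pairwise comparisons of the arms on both scales inflate the error further.** The Statistical analysis section plans no contrasts. If contrasts followed only a significant overall test, the rate with no effect anywhere could not exceed the 0.10 of step 2.
- **That FIM will hit its ceiling.** The article says "The maximum score is 126 and represents the total independence of the subject" and "Patients classified from stage I to stage III are defined as mildly disabled", but it gives no baseline FIM scores, and the second statement describes Hoehn and Yahr stages. A ceiling would in any case reduce power; it would not create false positives.
- **That UPDRS at discharge should be the sole primary.** Nothing in the article settles that choice, and its design and discussion also give weight to follow-up.

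**Conclusion.** The point holds in conditional form. As written, the plan leaves the success rule open and so does not guarantee a trial-level error of 0.05. If either scale can carry the claim, the error is up to 0.0975. It is about 0.08 to 0.097 for correlations of 0.3 to 0.8 (1.6 to 1.9 times 0.05) and about 0.07 at 0.9. If both must be significant, 0.05 is kept. These figures assume no effect on either scale, one overall test per scale at 0.05 (the natural reading, though not stated in words), and correlations that the article does not give. The planned sample size is not shown to be wrong.

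**What to change.** State the success rule in Outcome measures and protect the 0.05 in Statistical analysis. If another document already holds such a rule, repeat it in the article.

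- **Default: Holm across the two primary tests.** The smaller p-value is compared with 0.025; if it is significant, the other is compared with 0.05. Either scale can succeed alone. The cost is the first test at 0.025: power for one scale is about 0.83 to 0.85 at 80 patients with no dropout, and 0.72 to 0.74 at 64 completers. Keeping 80% needs 76 completers, which uses most of the dropout margin in 80. These figures rest on the between-group test with time correlation 0.75 to 0.80.
- **Alternative: a pre-specified order.** The first scale is tested at 0.05, and the second at 0.05 only if the first is significant. No alpha is split, but the second scale cannot succeed alone.
- **Alternative: both must be significant, each at 0.05.** No alpha is split, but power for joint success is lower. At 64 completers with f = 0.4 on both scales it would be 0.807² = 0.65 to 0.823² = 0.68 if the scales were independent, and higher with positive correlation.

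The change is a sentence in each of the two sections. The Sample size section should also say which rule and which per-test level the 80 patients are meant to support.

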### Unified Parkinson's disease rating scale (UPDRS)

The scale is divided into four macro-areas: 1. mental activities, behavior and mood; 2. activities of daily living; 3. motor assessment; and 4. complications. One of the main advantages of the UPDRS scale is that it provides a global assessment of the patient with Parkinson's disease, including both motor and non-motor aspects and any complications related to treatment. Other advantages of using this scale are its ease of use and speed of administration (53). It has also demonstrated excellent internal reliability (54), inter-rater validity (55), and good test-retest validity (56). From previous studies it seems that AOT has a significant impact on the functional recovery of PD patients (15).

### Functional independence measure

The FIM scale is widely used in rehabilitation settings to assess the level of assistance a patient needs in performing daily living activities. It includes 18 items with scores ranging from 1 to 7. The items are grouped into six areas, each with a specific competence: 1. self care; 2. sphincter control; 3. mobility; 4. locomotion; 5. communication; 6. social cognition. The maximum score is 126 and represents the total independence of the subject. The minimum score is 18 and represents the subject's total dependence in all activities of daily living (57, 58). It has good inter-rater reliability, although trained personnel are needed to administer it properly (59).

### Gait analysis

In addition to the two above-mentioned outcomes, in our study we will use gait analysis to assess kinematic parameters following the treatment. The Optoelectronic Motion Analysis System EL.I.TE (BTS, Milan, Italy) will be used for this evaluation (60–62).

### Data management

To ensure the anonymity of the participants enrolled in the study, each patient will be assigned an identification code. A list of identification codes will be then generated and stored separately. All descriptive data will be collected and stored on data files in protected computer networks.

### Statistical analysis

The statistical analysis of the data will be carried out by a statistician using the R software.

Given the design of the protocol (4 Groups X 3 Time-points), a mixed between-within ANOVA model with Greenhouse-Geisser correction will be used as a statistical test for this purpose. Statistical significance will be set at 0.05 to reject the null hypothesis.

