## Methods and analysis

### Study design

The aim of the study is to evaluate the efficacy of action-observation (AOT) and motor imagery (MI) treatment on the improvement of function and motility in patients with Parkinson's disease with a disease stage II or III according to Hoehn and Yahr. The study was approved by the ethical committee of the IRCCS Don Gnocchi, Milan. The study has been registered to clinicaltrial.gov with the Study ID number: AOTPRFDG. All procedure will be conducted according to the World Medical Association (WMA - 1996) and, when applicable, according to the procedure recommended by the Italian Association of Psychology (AIP). Before starting the study, each patient will be asked for written and verbal informed consent. Motor and functional assessments will be performed at T0 (baseline assessment)–T1 (4 weeks later, at discharge) and T2 (2 months after discharge, as outpatients).

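### The planned Greenhouse-Geisser ANOVA, as usually run, discards the T0 and T1 scores of any patient who misses T2; a likelihood-based repeated-measures model would keep them

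*Protocol article*

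**What the plan says.** Under Statistical analysis the protocol article fixes a single model: "Given the design of the protocol (4 Groups X 3 Time-points), a mixed between-within ANOVA model with Greenhouse-Geisser correction will be used". The only other rule there is the significance level: "Statistical significance will be set at 0.05 to reject the null hypothesis". Outcome measures makes score changes in FIM and UPDRS primary and names no primary time point.

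Study design places T1 at discharge from the four-week inpatient stay and the last assessment later, in a different setting: "T2 (2 months after discharge, as outpatients".

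Sample size derives 64 patients "with 80% power and 0.05 alpha in a mixed subjects design (4 groups and 3 time points", for an effect size of 0.4, and then plans 80, a number "that will be more than adequate to control for a potential" loss of participants. Over-recruitment is the only provision for dropout that the article describes.

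**The concern.** Mixed here means between-within factors, not a mixed-effects model. The Greenhouse-Geisser correction confirms this: its epsilon is estimated from the covariance matrix of complete patient vectors and belongs to the classical univariate repeated-measures ANOVA. Standard software for that test drops every patient who lacks one visit.

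T1 is measured before patients leave the ward, so it should be well captured. T2 requires them to come back two months later, so it is the visit most likely to be missed. Under the named method a missed T2 also removes that patient's T0 and T1 scores from the model. Two things are at stake: precision at discharge, and the protection that randomisation gives when those who return differ from those who do not.

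**Working it through.** **Inputs.** From Sample size: 64 required, 80 planned (20 per arm), effect size f = 0.4, 4 groups, 3 time points. From Study design: T1 at discharge, T2 two months later. Assumed, because the article gives no figure: the share missing T2, the within-patient correlation (rho), the true difference, and who misses T2.

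**The plan's own figures.** The step from 64 to 80 implies an allowance of 1 - 64/80 = 20%; conversely 64/(1 - 0.20) = 80. The 64 itself is not fixed by the stated inputs. With the between-groups test, lambda = f²·N·m/(1 + (m - 1)·rho), it needs rho of about 0.75 to 0.80; at rho = 0.75, lambda = 0.16·64·3/2.5 = 12.3 and power is 82.3%. That is a separate matter, and nothing below depends on it.

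**Precision.** If every loss occurs at T2, all 80 patients have T0 and T1, but the completer ANOVA uses only those with T2. The standard error of the T0-T1 contrast is multiplied by sqrt(80/n):

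| Assumed T2 loss | n kept | sqrt(80/n) |
|---|---|---|
| 10% | 72 | 1.054 |
| 20% | 64 | 1.118 |
| 30% | 56 | 1.195 |

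In SD units, with rho = 0.7, the variance of a change score is 2(1 - 0.7) = 0.6. The standard error of a two-arm difference is then:
- 20 per arm: sqrt(0.6·2/20) = 0.245
- 16 per arm: sqrt(0.6·2/16) = 0.274
- 20 per arm with baseline as covariate: sqrt((1 - 0.49)·2/20) = 0.226

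Keeping the patients takes 0.274 to 0.245. The further step to 0.226 comes from baseline adjustment and accounts for 0.019 of the total 0.048, about 40%.

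**Bias.** One simulation used 20 per arm, rho 0.6, a true T1 difference between combined arm and control of 0.80 SD, and 4,000 trials per row. Under selective loss, the chance of missing T2 rose as the observed T0-T1 change got poorer (logistic, slope 2 per SD).

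| T2 loss | Difference at T1, all patients | Difference at T1, completers |
|---|---|---|
| Random, 10% | 0.796 | 0.798 |
| Random, 20% | 0.807 | 0.808 |
| Random, 30% | 0.793 | 0.792 |
| Selective, about 18% | 0.799 | 0.643 |
| Selective, about 27% | 0.796 | 0.600 |
| Selective, about 35% | 0.802 | 0.575 |

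Random loss causes no bias. At 20% the spread of the estimates rises from 0.284 to 0.318, a ratio of 1.12, which agrees with the formula. Selective loss shrinks the estimate although every T1 value was observed.

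A second set-up (rho 0.7, true difference 0.75 SD, about 22 to 27% selective loss) gives completer estimates of roughly 0.63 to 0.69. That is 0.06 to 0.12 too small: 0.06/0.75 = 8% to 0.12/0.75 = 16%. The result depends on the assumed slope: gentler and steeper choices moved it between 0.72 and 0.60. Using all observed T1 data returns 0.75.

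**The case against.** The strongest reply is that the article nowhere says completers or listwise. Deletion is inferred from how the named method is usually run. Imputing before the ANOVA would be compatible with the text and would keep every patient, and an article may leave that step to a fuller document. This stands as a limit on certainty: a reader might infer that the plan prescribes a completer analysis, and it does not. The point survives because the named method is specific, and an analysis that follows it in the ordinary way loses these records.

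Nor is a separate discharge test stated. The discharge comparison here means the T0-T1 part of the single 4 x 3 model, and a T0-T1 contrast on everyone seen at T1 is not ruled out. Patients who leave during the inpatient stay have no T1 value for any model to use.

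A reader might also infer that the trial would become underpowered. A one-way test on the discharge change at f = 0.4 does fall from 84.5% power with 80 patients to 74.2% with 64. The plan does not state that test. On its own basis 64 patients give 80% power, so losing 16 of 80 leaves its target intact.

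Finally, a bias of 0.06 to 0.12 is well under one standard error of about 0.27. That is true of any single trial result, but the bias has a direction and is not removed by recruiting more patients.

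**Conclusion.** The point holds in a limited form. The only analysis named for the primary outcomes, in its usual implementation, throws away observed discharge data from patients who miss T2, and over-recruitment does not repair the comparison between randomised groups.

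The certain cost is precision: about 12% on the standard error of the T0-T1 contrast if 20% miss T2, a rate inferred from 64 and 80. Bias is conditional. There is none if loss is random. If poor responders are likelier to stay away, the illustrations show a true 0.75 SD estimated at roughly 0.63 to 0.69, depending on an assumed slope. Nothing in the article says who will miss T2, so the documents do not support a claim that the result will be biased. This should be fixed, but it does not invalidate the trial.

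**What to change.** Make the primary analysis of FIM and of UPDRS a likelihood-based linear mixed model for repeated measures. Fit it to all observed data from all randomised patients, each in the assigned arm. Keep the Greenhouse-Geisser ANOVA on completers as a sensitivity analysis. Entering baseline as a covariate is a separate option that adds precision; the defect does not require it.

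The cost is a change of wording. The model runs in R, which is already planned, and needs no further patients or visits. There are two small downsides. The likelihood model still assumes that data are missing at random given what was observed, and this should be stated. The change must also be made before the data are analysed, so that the choice of primary model cannot appear to depend on the results.

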Based on those evidence, we came up with the concept of evaluating the effectiveness of these two cognitive strategies, motor imagery and action observation, in the rehabilitation of Parkinson's disease patients. Based on the ongoing debate and the evidence that action observation is more effective than motor imagery in learning a novel, complex motor task in healthy individuals (37), the first point we want to assess is whether Motor Imagery and action observation are similarly effective, when taken alone, in Parkinson's disease patients. Second, this study aims to assess whether the combination of the two is more effective than the individual treatments. In fact, recent evidence show that motor performance is improved when motor imagery is associated with synchronous action observation of the imagined actions (38).

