## Discussion

AOT and MI are two cognitive strategies useful in neuro-rehabilitation. In the literature, there are only preliminary evidence in favor of their effectiveness in the motor recovery of patients with Parkinson's disease. However, there is still little evidence as to which of the two strategies is best for this purpose or whether, combining the two, the benefits for patients can be maximized. In healthy participants by comparing these two strategies, it has been found that Action-Observation is more effective than MI in improving the learning of complex novel motor tasks (37). This greater effectiveness may derive from various factors, one of which may be linked to the method itself. While during observation the motor task shown is contextualized and performed “correctly”, in motor imagery the effectiveness depends, in part, also on the participant's ability to re-enact that specific action in a proper manner. When applying these strategies in neuro-rehabilitation it's worth stressing that during action observation, at difference with motor imagery, the clinician has greater control over the attention, motivation and correct execution of the task by the participant throughout the treatment. We expect that this study will bring further evidence in understanding which of the two strategies is more effective in the rehabilitation of Parkinson's Disease patients and whether combination of the two methods may be more effective than the single ones.

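### The one stated test, an omnibus 4 × 3 mixed ANOVA with no deciding effect or contrast named, does not match the between-arm questions the article asks

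*Protocol article*

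**What the plan says.** The Statistical analysis section of the protocol article gives a single procedure. For the design of four groups by three time points, "a mixed between-within ANOVA model with Greenhouse-Geisser correction will be used as a statistical test for this purpose", and "Statistical significance will be set at 0.05 to reject the null hypothesis". It does not say which null hypothesis is meant, which of the model's effects decides, or which arms are compared.

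The questions are stated elsewhere:

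- The Introduction asks first "whether Motor Imagery and action observation are similarly effective, when taken alone", and second "whether the combination of the two is more effective than the individual treatments".
- The Discussion repeats the second: "whether combination of the two methods may be more effective than the single ones".
- The Study design section adds a general efficacy aim for AOT and MI, and the Discussion adds long-term effect against conventional rehabilitation.

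The Outcome measures section defines the primary outcomes as score changes on FIM and UPDRS. The Sample size section powers the trial for an overall f of 0.4 with four groups and three time points, again without naming the effect tested.

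**The concern.** The model yields three F tests: Group (3 df), Time (2 df) and Group × Time (6 df). The two questions in the Introduction are three single-df comparisons: AOT minus MI, AOT+MI minus AOT, and AOT+MI minus MI. None of the F tests is any of these.

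A significant omnibus result says that some arms differ in some way over time, not which arms or when. Followed as written, the analysis could return a positive result that leaves both questions open. They would then be settled by pairwise tests chosen after the data are seen. Three unadjusted pairwise tests at 0.05 on one outcome carry a family-wise error of about 12% (simulated), and there are two primary outcomes.

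**Working it through.** **Inputs.** From the article: four arms, three visits (T0, T1, T2), alpha 0.05, f = 0.4, 80% power, N = 64 (16 per arm), planned N = 80 (20 per arm). Assumed, because the article gives none: SD 1 at every visit, equal correlation ρ between visits (0.5 and 0.8 shown), and the size and pattern of the effect.

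**1. The article's own N = 64.** For the Group main effect, λ = f²·N·m/(1 + (m − 1)ρ), with m = 3 and df 3 and N − 4.

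- ρ = 0.75: λ = 0.16 × 64 × 3/2.5 = 12.29, power 82.3%.
- ρ = 0.80: λ = 30.72/2.6 = 11.82, power 80.7%.
- ρ = 0.50: 52 patients would be enough.

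For the interaction, the same f at ρ = 0.5 needs only 20 patients. Under the alternative effect-size convention (partial eta-squared, as in SPSS) it needs 52, 60 or 76, for a sphericity correction of 1, 0.75 or 0.5. So 64 is reachable, but only with unstated inputs. It is neither confirmed nor refuted, and it does not reveal which effect was meant.

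**2. Does a significant Group × Time result answer the questions?** Let AOT, MI and AOT+MI all improve by 0.8 SD at T1 and T2, and Control by nothing. All three differences that the Introduction asks about are then zero.

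- Deviations from the mean of the arms at T1 and T2: +0.2 for each active arm, −0.6 for Control. Sum of squares = 3 × 0.04 + 0.36 = 0.48.
- Time pattern (0, 1, 1), centred: (−2/3, 1/3, 1/3). Sum of squares = 2/3.
- λ = n × 0.48 × (2/3)/(1 − ρ), df 6 and 2(N − 4).

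| n per arm | ρ | λ | Interaction significant |
|---|---|---|---|
| 16 | 0.5 | 5.12/0.5 = 10.24 | 63% |
| 16 | 0.8 | 5.12/0.2 = 25.6 | 98% |
| 20 | 0.5 | 6.4/0.5 = 12.8 | 75% |
| 20 | 0.8 | 6.4/0.2 = 32.0 | 99% |

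Simulation of the mixed ANOVA with the Greenhouse-Geisser correction (3,000 runs per row) agrees: 63%, 98%, 75% and 99%.

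**3. The two main effects.** The Group effect averages in the pre-treatment visit. A true f of 0.4 at T1 and T2 shrinks to 0.4 × 2/3 = 0.267, which at N = 64 gives power of 55% (ρ = 0.5) or 43% (ρ = 0.8). The Time effect reacts to improvement shared by all arms: with a common gain of 0.3 SD and no arm difference, it is significant in 68% to 99% of simulated trials (n = 16 and 20, ρ = 0.5 and 0.8). Under the same common gain the interaction stays near 5%.

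**4. Power of the contrasts themselves.** The article gives no pairwise difference. For a two-sided t test with n per arm, the noncentrality is d√(n/2). At an assumed d = 0.8, before baseline adjustment:

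- n = 16: 0.8 × √8 = 2.26; power 59% unadjusted, 41% with Bonferroni for three.
- n = 20: 0.8 × √10 = 2.53; power 69% and 52%.

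**5. Power of the interaction against a baseline-adjusted 3-df comparison at T1**, with f = 0.4 at T1 and N = 64:

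| Pattern at T2 | ρ | Group × Time | T1 ANCOVA |
|---|---|---|---|
| Sustained | 0.5 | 78% | 86% |
| Halved | 0.5 | 63% | 86% |
| Sustained | 0.8 | over 99% | over 99% |
| Halved | 0.8 | 98% | over 99% |

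**The case against.** The other side has good points.

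- **The model can supply the contrasts.** A mixed ANOVA is not wrong in itself, and a journal article may leave follow-up comparisons to an analysis plan that is not shown. This stands against any claim that the model cannot answer the questions. It does not remove the mismatch: the article does state its test, and the stated test is not aligned with its stated aims.
- **The intended test is probably the interaction.** A reader might infer that the trial could be declared positive on a time trend alone. The documents do not support that. The outcomes are score changes, the questions compare arms, and the model is introduced by its group-by-time layout, all of which point to Group × Time. Nowhere does the article treat a Time effect as efficacy. The Time and Group figures in step 3 are therefore reasons to name the effect, not a forecast of what the authors would claim. The case in step 2 grants the interaction reading and still holds.
- **Control and long-term comparisons are also aims.** It is tempting to say that the omnibus test spends power on patterns nobody asked about. The Study design section and the Discussion contradict that. An interaction driven by Control bears on the general efficacy aim, though not on the two questions in the Introduction.
- **Power.** A reader might infer that the omnibus test is clearly the weaker one. Step 5 shows a loss at ρ = 0.5 and almost none at ρ = 0.8. The comparator there is itself a 3-df test, so it says nothing about single contrasts.

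**Conclusion.** The point holds as a mismatch between test and aims. The article fixes one omnibus test with no deciding effect and no contrast named. Even on the most favourable reading, a significant result does not answer whether AOT and MI differ or whether the combination beats either. When every difference in question is zero and only Control lags by 0.8 SD, the interaction is significant in about 63% to 98% of trials at N = 64. These figures rest on an assumed gap, a sustained effect, equal correlations of 0.5 to 0.8 and no missing data. The logical point rests on none of them.

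The conclusion does not extend to saying that the ANOVA is invalid, that N = 64 is wrong, or that contrasts would always gain power.

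**What to change.** In the Statistical analysis section:

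1. State that efficacy is judged on between-arm differences in change, not on the Time or Group main effect.
2. Pre-specify baseline-adjusted contrasts at a named time point, each with a 95% confidence interval: AOT minus MI, AOT+MI minus AOT, and AOT+MI minus MI. Claim that the combination is better only if both of its contrasts are significant in its favour.
3. Control multiplicity across the two questions. Holm would serve, using the p-value for AOT minus MI and the larger of the two combination p-values.
4. Keep the contrasts against Control and the T2 contrasts as planned analyses, because the Study design section and the Discussion ask about them. Which time point is primary is the sponsor's choice.
5. State that a non-significant AOT minus MI contrast will not be read as showing the two to be alike, and that its confidence interval will be interpreted instead.

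The cost is some wording and a few lines of R, with no new patients or data. The downside is that fewer comparisons are confirmatory and each has limited power (step 4). Requiring both combination contrasts to succeed lowers the chance of that claim further. Baseline adjustment recovers some power, by an amount that depends on the unstated correlation.
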